The protocol, informed consent form(s), recruitment materials, and all participant materials will be submitted to the IRB for review and approval. Approval of both the protocol and the consent form(s) must be obtained before any participant is consented. Any amendment to the protocol will require review and approval by the IRB before the changes are implemented to the study. All changes to the consent form(s) will be IRB approved; a determination will be made regarding whether a new consent needs to be obtained from participants who provided consent, using a previously approved consent form.

# PROTOCOL SUMMARY

## Synopsis

| **Title:** | Skills to Enhance Positivity in Adolescents at Risk for Suicide |
| --- | --- |
| **Grant Number:** | MH123556-01A1 |
| **Study Description:** | The purpose of this study is to examine the effectiveness of the Skills to Enhance Positivity (STEP) intervention in reducing suicidal behaviors in adolescents who have been admitted to an inpatient psychiatric unit due to suicide risk. |
| **Objectives:** | Primary Objective: Examine the effectiveness of STEP in reducing suicidal events (suicide attempt or emergency intervention to intercede attempt), active SI (with intent or plan), and depression at 6-month follow-up (primary endpoint outcomes) and suicidal events at 12-month follow-up (distal, endpoint outcome).  Secondary Objective: Examine engagement of the hypothesized mechanisms (attention to positive and negative affect) at the 3- and 6-month follow-up.  Tertiary Objective: Examine whether hypothesized mechanisms mediate reduction of suicidal events and ideation. |
| **Endpoints:** | Primary Endpoint: Suicidal events, active suicidal ideation, and depression at 6 month follow-up.  Distal Primary Endpoint: Suicidal events at 12 month follow-up.  Secondary Endpoint: Attention to Positive Affect and Negative Affect at 6 month follow-up. |
| **Study Population:** | Adolescents, regardless of sex, gender, race, and ethnicity, between the ages of 12-18, who have been hospitalized due to suicide risk (i.e., a suicide attempt or suicidal ideation) will be recruited for study participation from three adolescent units at Boston Children’s Hospital (Boston, MA), Butler Hospital (Providence, RI), & Bradley Hospital (Providence, RI). Target recruitment is 216. |
|  |  |
| **Phase or Stage:** | Phase III |
| **Description of Sites/Facilities Enrolling Participants:** | Three sites, all in the United States, will be enrolling participants: 1) the adolescent inpatient unit at Boston Children’s Hospital; 2) the adolescent unit of Butler Hospital; and 3) the adolescent inpatient unit at Bradley Hospital |
| **Description of Study Intervention/Experimental Manipulation:** | The study intervention, Skills to Enhance Positivity (STEP), is an adjunctive psychosocial intervention that involves 4 in-person session (4 individual) during a participant’s inpatient admission, followed by three months of text or email messaging for mood monitoring and skills delivery. The sessions and skills delivered via the messaging focus on the functions of positive affect and ways to bring greater attention to and awareness of positive emotions and experiences on a daily basis. |
| **Study Duration:** | 36 months |
| **Participant Duration:** | 12 months |

## Schema

***Flow Diagram for Randomized Clinical Trial***

Pre-screen potential participants by inclusion and exclusion criteria via chart review.

Pre-Screening

Day -30 to

Day 1

Conduct informed consent and assent process. Perform baseline assessments.

(N = 216)

Refer to **Section 1.3, Schedule of Activities**>

Baseline

Day 1

Randomize

Administer study interventions Session 1-4; Provide parent infographic

Sessions

During Inpatient

Hospitalization

Day 1 ± 14

Remote delivery

Remote delivery of skills messages / reminders via text or email

via text or email

*Post-discharge to

3 months

Post-Intervention assessments

Post intervention

assessment

*Day 97 ± 14

Follow-up assessments

6 month follow-up

*Day 182 ± 14

**Final Assessments**

Refer to **Section 1.3, Schedule of Activities**>

12 month follow-up

*Day 365 ± 14>

* Anchored to discharge date

## Schedule of Activities

| **TABLE OF ASSESSMENTS** |  |  |  |  |  |  |
| --- | --- | --- | --- | --- | --- | --- |
| **Instrument** | **Admin to:** | **Type** | **Base** | **3M** | **6M** | **12M** |
| **Demographics** | A, G | Interview | X |  |  |  |
| **Suicidal and Self-Harm Behaviors:** |  |  |  |  |  |  |
| Columbia Suicide Severity Rating Scale (C-SSRS) | A, G | Interview | X | X | X | X |
| Suicide Ideation Questionnaire (SIQ) | A | SR | X | X | X |  |
| Suicidal Ideation Psychiatric Rating Scale – Longitudinal Follow-up Evaluation (LIFE-SI-PSR) | A | Interview | X | X | X |  |
| Functional Assessment of Self-Mutilation (FASM) | A | SR | X | X | X |  |
| **Diagnostic / Symptom Rating Scales:** |  |  |  |  |  |  |
| Beck Depression Inventory (BDI-II) | A, G | SR | X | X | X |  |
| Alcohol Use Disorder Identification Test (AUDIT) | A, G | SR | X | X | X |  |
| Drug Use Disorder Identification Test (DUDIT) | A, G | SR | X | X | X |  |
| Borderline Evaluation of Severity Over Time (BEST) | A, G | SR | X | X | X |  |
| Columbia Impairment Scale (CIS) | A, G | SR | X | X | X |  |
| **Treatment Targets of STEP:** |  |  |  |  |  |  |
| Attention Dot Probe Positive and Negative Stimuli | A | Task | X | X | X |  |
| Implicit Positive and Negative Affect Test | A | Task | X | X | X |  |
| Modified Differential Emotions Scale (mDES) | A | SR | X | X | X |  |
| Satisfaction with Life Scale (SWLS) | A | SR | X | X | X |  |
| Gratitude Questionnaire (GQ-6) | A | SR | X | X | X |  |
| **Ancillary Treatment Received:** |  |  |  |  |  |  |
| Treatment History Interview | A, G | Interview | X | X | X |  |
| Medication Compliance Questionnaire | A, G | Interview | X | X | X |  |
| **Implementation:** |  |  |  |  |  |  |
| Client Satisfaction Questionnaire | A, G | SR |  | A, G |  |  |
| Acceptability of Intervention Measure (AIM) | A, G | SR |  | A,G |  |  |
| Intervention Appropriateness Measure (IAM) | A, G | SR |  | A,G |  |  |
| Feasibility of Intervention Measure (FIM) | A, G, P (at different timepoints) | SR | P | A, G |  | P |
| Qualitative Exit Interviews | A, G, P (at different timepoints) | Interview | P | A, G |  | P |
| Evidenced Based Practice Attitude Scale (EBPAS) | P | SR | P |  |  | P |
| Implementation Climate Scale | P | SR | P |  |  | P |
| Implementation Readiness Scale | P | SR | P |  |  | P |

***X denotes administration of that instrument***

**A = Adolescent; P = Provider; G = Guardian; SR = Self-Report**

**Guardians will be asked to assess and report on adolescents (not self-report) using the instruments listed above****

# INTRODUCTION

## Study Rationale

Suicide and suicidal behavior in adolescents have been steadily increasing over the past two decades. Unfortunately, reviews of published randomized controlled trials (RCTs) for adolescent suicidality conclude that treatments to date have been minimally efficacious, particularly when compared to adult trials. The preponderance of interventions focus on crisis intervention, underling psychiatric disorders, regulating negative affect, and reducing cognitive distortions. However, our pilot work and other recent data suggest the importance of considering how *low positive affectivity* *may be a mechanism that contributes to suicidal behaviors independent of other risk factors.* Therefore, we developed an intervention, *Skills to Enhance Positivity* (STEP; MH R34101272), premised on the Broaden and Build theory of positive affect, to increase attention to, and awareness of positive affect and experiences. Results from our pilot RCT (N=52) with inpatient suicidal adolescents found that compared to a Healthy Habits / Enhanced Treatment as Usual (ETAU) condition, those randomized to STEP had 50% fewer individuals reporting a suicide event, 50% fewer suicidal events overall, and a larger decrease in participants reporting active suicidal ideation (SI) over follow up (f/u) (49% STEP vs. 19% ETAU). STEP also appears to have engaged the target mechanism as STEP participants had faster reaction times to positive probes on an attentional bias task compared to ETAU.

These promising results in which we were able to demonstrate engagement of the target (positive affect) and a decrease in clinical outcomes (suicidal events) suggest the need to test the clinical effectiveness of STEP by having clinical staff implement the intervention. Furthermore, recognizing the need to speed translation, we propose a Hybrid Type I Effectiveness-Implementation design. Specifically, we propose to test the effectiveness of STEP in reducing suicidal events and ideation in 216 adolescents, admitted to inpatient psychiatric care due to suicide risk. Participants will be randomized to either STEP or ETAU. STEP involves 4 in-person sessions focused on psychoeducation regarding positive and negative affect, mindfulness meditation, gratitude, and savoring. Parents will also be provided with a handout containing study contact information and key information on how parents/guardians can best support their children throughout the study. 4 videos with content covered in the treatment manual will be used to supplement the skills taught during the 4 in-person STEP sessions. Mood monitoring prompts and skill reminders will be sent daily for the first month post-discharge and three times a week for the following two months. The ETAU condition will receive text or email reminders to visit their safety plan or practice a Healthy Habit, matched in frequency to the STEP group. Effectiveness aspects of the design include using clinical staff as interventionists and having very few exclusion criteria.

The public health significance of this application is evident as it addresses the Healthy People 2020 Objective MHMD HP 2020- 2: “Reduce suicide attempts by adolescents.” This application also strongly aligns with NIMH’s interest in improving post-acute care and optimizing longer term outcomes (PAR-18-430), as well as the NIMH 2020 Strategic Plan for Research, specifically objective 3.3. “test interventions for effectiveness in community practice settings” and 3.3.c “enhancing the practical relevance of effectiveness research via deployment-focused hybrid effectiveness-implementation studies”.

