Our data also suggest that STEP engaged the target of PA. On the attentional dot probe task using words, groups did not differ at baseline or post treatment. However, a significant between group difference was found with those in the STEP condition showing more attention biased toward happy words at the 3-month f/u compared to the ETAU group, *t*(34) = 2.06, *p* = .048, η^2^ = .04. While our self-report assessments did not yield any significant between-group differences, stronger pre-post effects (from baseline to post-tx, and baseline to f/u) were observed in STEP on *gratitude* and *satisfaction with life*, with significant within group comparisons observed in STEP but not in ETAU for 3 out of 4 comparisons (effects sizes (Cohen’s *d*) ranging between 0.59-0.87). Furthermore, mood responses based on the six Modified Differential Emotions Scale (mDES)(25) items delivered daily to STEP participants, suggested that in 400 total days of full reporting (58% of surveyed days), 84% of STEP participants reported more days in which their PA > NA. We also observed a strong within-group effect on our secondary mechanism of negative affect for those in STEP (d = 1.01), although there was no statistically significant difference between groups. Finally, we have data supporting our hypothesized mechanisms are related to suicide outcomes. *Satisfaction with Life* at post-treatment predicted SE and active SI at the 6 month f/u, and these measures at the 3 month f/u, predicted SE at 6 month f/u. Adjusting for direction of effects, odds ratio (*OR)* ranged from 1.10 to 1.17; p = .04 to .003, respectively. Furthermore, PA (mDES) at 3 month f/u predicted 6 month active SI (adjusted OR = 2.33; p = .03), and NA (mDES) at post-treatment and 3 month f/u predicted 6 month SE and active SI (OR ranged from 2.69 to 4.94; p = .02 to .004).

These preliminary data importantly demonstrate the feasibility, and our capability, of mounting a large-scale trial and implementation study of the STEP intervention. We have the capacity to recruit adolescents, and to engage them in STEP. We also show evidence of efficacy and engagement with the target, although we recognize that the small sample size of the pilot trials leads to low precision of these effect size estimates.

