***Remote delivery phase.*** The remote delivery phase of STEP begins immediately after discharge. All participants will be asked to take a photo of their safety plan and to have phone numbers of supportive resources stored into their contacts. Those randomized to STEP will be sent an automated sequence of text messages, starting with a password entry as an additional confidentiality safeguard. They are then asked to complete a set of 6 mood monitoring questions from the mDES (e.g., “*How glad, happy, joyful, do you feel RIGHT NOW? Enter any # from 1 to 5 (1 = not at all, 5 = extremely*)”), followed by a request for the participant to select the type of exercise (i.e., mindfulness meditation, gratitude, or savoring) that they would like to practice *(“Choose the type of message you would like to receive right now: 1 = mindfulness; 2 = gratitude; 3 = savoring”)*. In response, the participant will receive a corresponding exercise to practice (e.g., “*share something positive with a friend or family member*”). Participants will also be asked if they had practiced a positive affect exercise the preceding day. If the participant does not respond after 2 alerts, a random exercise practice reminder will be automatically sent from a bank of exercise reminders. Therefore, participants will always receive a reminder to practice a positive affect exercise regardless of whether or not they engaged with the program. These procedures are the same as the pilot RCT, in which we have demonstrated feasibility of the approach. No questions about SI will be asked; nonetheless, a message will be displayed to let users know that no one is reading their responses and that if they are experiencing a mental health crisis, to contact their provider and/or Emergency Department. After the 30 days of daily practice reminders, participants will be placed on a tapered schedule of three times per week for an additional 60 days. After that time, they will no longer receive alerts.

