The comparison condition consists of treatment as usual on the unit which is enhanced by asking participants to take a photo of their safety plan to store on their phone, and to ask participants to store phone numbers of supportive contacts on their phone. Participants will receive texts or emails on a daily basis for 30 days with reminders to check their safety plan and other healthy habit reminders. This procedure helps control for contact time by equating the two conditions. Unlike the STEP condition they will not receive the mood monitoring questions or positive affect skills as these are conceptualized as part of the study intervention. ETAU participants will be placed on a tapered schedule of receiving alerts 3 times per week for an additional 60 days. After 3 months, they will no longer receive alerts.

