Subjective Positive and Negative Affect. Self-report ratings of PA and NA will be assessed at baseline, 3-, 6-, and 12-month f/u, through the *Modified Differential Emotions Scale* (mDES)(25). The 19-item mDES assesses short-term state positive and negative emotions, along a 5-point Likert scale. Each item consists of three related terms to describe a particular discrete emotion (e.g., glad, happy, joyful). Participants will be asked to rate each set of emotions based on how they were feeling “right now.” The Positive Emotions subscale is a composite of 10 items, while the Negative Emotions subscale is a composite of 9 items. The scale has psychometric support (25) and in the pilot sample, Cronbach’s α was = .86 and .92 for the positive and negative emotions subscales, respectively. To obtain subjective indices of eudemonic (i.e., sustainable) positive affect, we will administer the *Gratitude Questionnaire* (*GQ6*) (61, 62) and the *Satisfaction with Life Scale* *(SWLS)* (63). Both scales use a 7-point Likert response format and will be administered only to the adolescent.

Ancillary Treatment. To assess ancillary treatment, we will administer the Child and Adolescent Services Assessment Screen (CASA) which is a self-report measure at 3-, 6-, and 12-month follow-up, and administer the Treatment History Interview and the Medication Compliance Questionnaire (MCQ), both interviews, at baseline and 3-, 6-, and 12-month follow-up.

Implementation. Implementation Evaluation is based on Proctor et al.’s (64) categorization of implementation outcomes. This study will measure: 1) acceptability, or the extent to which adopting STEP is agreeable, palatable, or satisfactory among key stakeholders, 2) appropriateness, the perceived fit, relevance or compatibility of STEP for a given setting, provider or family; and 3) feasibility, the extent to which STEP can be successfully used or carried out within a given setting. These will be examined using the Acceptability of Intervention Measure (AIM), Intervention Appropriateness Measure (IAM), and the Feasibility of Intervention Measure (FIM), after all post-treatment data have been collected (65). Each are 4-item scales that have demonstrated good psychometric properties including good test-retest reliability and discriminant validity (65).

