handled with multiple imputations, with assumptions checked with sensitivity analyses (76), is pre-specified (as are all aspects of our analysis plan). We will adhere to intent-to-treat principles, and all aspects of data analysis will be pre-specified as reflected in this proposal, and with modification following proposal review and discussions with program and our Data Safety and Monitoring Board. Preliminary analyses will include descriptive statistics to examine the distributional and psychometric properties of the variables (e.g., normality, internal consistency). Variables will be transformed to better approximate normality if this is necessary given the observed distribution and the assumptions of the analysis model. We will also examine post-inclusion attrition by comparing study completers to dropouts on sociodemographic, baseline data, and psychotropic medication usage to determine if they differ systematically. We will examine the success of the stratified randomization by examining between-group differences at baseline. Preliminary analyses may also include analyses of adverse events, the progress of recruitment and retention, and data processing and quality markers as the study progresses. Daily mood monitoring data is not included in outcome analyses because it is conceptualized as part of this adjunctive intervention and only collected in one condition.

Missing data. To accommodate attrition and other sources of missingness, we will utilize the method of multiple imputation by chained equations. At least 50 replicates of each missing value will be generated for inclusion in analyses. This method can accommodate clustering of repeated measures at the level of the. We have previously used these methods in successful analyses of trials of exercise interventions.

Statistical computing. Modeling will be performed using Stata (Stata Corp, College Station, TX, version 16.2 or higher) and R software (R Foundation for Statistical Computing, Vienna, Austria, version 4.0 or higher) and Mplus (version 8.4 or higher, Muthen & Muthen, Los Angeles, CA). Analyses and reporting will be executed and archived to ensure full replicability and reproducibility by analysts at Brown University, under the direction of the project methodologist, [name].

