**Aim 2:** *Examine engagement of the hypothesized mechanisms at the 3- and 6-month f/u.* We hypothesize that those randomized to STEP, compared to ETAU, will have*:* **H2A:** higher attention to positive affect, assessed by implicit tasks; **H2B**: Increased gratitude and satisfaction with life, assessed by self-report; **H2C**: lower attention to negative affect, assessed by implicit tasks and self-report. Aim 2 analyses will use a repeated measures design and a multilevel or mixed effect modeling framework. For H2A, H2B, and H2C, the outcomes are continuous and a mixed effect general linear model will be used. Outcomes are repeatedly observed over follow-up and assessed at the scheduled follow-up (3M, 6M). For all hypotheses, we will treat the individual as the random effect. Treatment effects will be estimated as the weighted average of the differences between ETAU and STEP groups overall follow-up times, adjusting for follow-up time. ***Sample size and statistical power considerations***: As with H1, we determined minimal detectable effect sizes using Monte Carlo methods. This involved generating 1,001 simulated data sets representing our hypothesized effects, and our assumptions of a 10% loss by 3M and another 10% loss by 6M follow-up. We assumed repeated measures of the measures assessing the mechanisms (attention to positive affect, gratitude and satisfaction with life, and attention to negative affect) to have a stronger correlation within a respondent over time than the Aim 1 outcomes, and assumed *r* = .75, which results in a smaller effective sample size. Across the simulated data sets, we compute power as the proportion of replicates returning a significant effect in the hypothesized direction. Results of these models are summarized in Table 3, above. We summarize effects in terms of Cohen’s effect size statistics for clear expression of the minimum detectable effects. For Aim 2 outcomes, we will have sufficient power to detect small-to-medium effect sizes (*d* = .39).

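### Six mDES items are texted to STEP participants only and scored again in the 3M and 6M mDES, so a self-report affect difference could partly reflect item familiarity

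*Protocol*

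**What the plan says.** The prompt schedule is in Study Rationale ("Mood monitoring prompts and skill reminders will be sent daily for the first month post-discharge and three times a week" for the next two months) and again under Administration and/or Dosing: 30 days daily, then three times a week for 60 days. That section gives the content of the STEP prompts: "They are then asked to complete a set of 6 mood monitoring questions from the mDES". Its printed example is a triplet of emotion words, rated for the present moment from 1 to 5. Of ETAU it says: "Unlike the STEP condition they will not receive the mood monitoring questions or positive affect skills". ETAU messages match STEP in frequency but not in content.

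The outcome instrument is the 19-item mDES (10 positive and 9 negative items, 5-point scale), described under Endpoint and Other Non-Safety Assessments. Its items are triplets too, and the time frame is again the present moment: "Participants will be asked to rate each set of emotions based on how they were feeling" right now. The Schedule of Activities lists it under the treatment targets of STEP, at baseline, 3M and 6M. Objectives and Endpoints counts self-report forms within the secondary endpoint, with 3M primary. Aim 2 states H2C as "lower attention to negative affect, assessed by implicit tasks and self-report". Aim 3 takes negative affect at 3M as a mediator of 6M outcomes.

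Statistical Considerations addresses part of the matter: "Daily mood monitoring data is not included in outcome analyses because it is conceptualized as part of this adjunctive intervention", and because the ratings exist in one condition only.

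**The concern.** The protocol recognises that the daily ratings belong to the intervention and cannot be compared between arms. But the items behind those ratings return inside the scheduled outcome. By 3M, STEP participants will have answered these six items many times, whereas ETAU participants will have met them once, at baseline. Repeated answering may change how an item is answered (habituation, a changed use of the scale, a wish to show progress) without any change in affect. Leaving out the daily data does not undo that.

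The stake is interpretation. Aim 2 would read a STEP–ETAU difference on the mDES as engagement of the mechanism, and Aim 3 could carry it into a causal path. The mDES is the only scheduled instrument that the protocol describes as a self-report of negative affect, so the self-report part of H2C depends on it. The 3M visit, the main time point for engagement and mediation, comes about a week after the texts stop (day 97 ± 14 against about day 90).

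**Working it through.** The protocol states no count of prompts or answers, so there is no figure of its own to reproduce on exposure.

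**Exposure before 3M**
- Scheduled prompts: 30 + 3 × 60/7 = 55.7.
- Pilot rates (Background): a response to the text component on 70% of days in the pilot RCT; full mDES reporting on 58% of surveyed days.
- Daily month only: 30 × 0.58 = 17.4; 30 × 0.70 = 21.0.
- Whole schedule, if the rates hold through the taper: 55.7 × 0.58 = 32.3; 55.7 × 0.70 = 39.0.
- ETAU: 0.
- Limit on the larger counts: 400 full days at 58% means 400/0.58 ≈ 690 surveyed days, or 690/26 ≈ 27 per STEP participant if all 26 are counted. The 58% therefore seems to describe roughly the first month. The 70% is any response, not completion of the mood items.

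**How far a shift on the monitored items would move the 9-item negative subscale**
- Mean inter-item correlation from the pilot alpha: r = α/(k − (k − 1)α) = 0.92/(9 − 8 × 0.92) = 0.561.
- SD of the subscale mean, in item-SD units: √((1 + 8 × 0.561)/9) = 0.781.
- Assumed, not in the protocol: m = 2 to 4 of the six items are negative; each shifts by s = 0.2 to 0.5 SD in STEP's favour with no change in affect.
- Subscale shift = (m/9) × s/0.781. For (2, 0.2): 0.057 SD. For (3, 0.3): 0.128 SD. For (4, 0.5): 0.285 SD.

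**Chance of a false favourable result** (two-sided 5%, so 2.5% in this direction with no artefact)
- Precision is taken from the stated detectable effect d = .39, read as 80% power: z = 2.802 × shift/0.39, and probability = 1 − Φ(1.96 − z). The .39 is plausible: two measures correlated at .75 with 10% + 10% loss give a detectable d of about 0.38.
- Aim 2 estimates a weighted average over 3M and 6M, so two extremes are shown. The second halves z (no artefact at 6M, equal weights).

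| m, s | z | artefact persists to 6M | faded by 6M |
|---|---|---|---|
| 2, 0.2 | 0.41 | 6% | 4% |
| 3, 0.3 | 0.92 | 15% | 7% |
| 4, 0.5 | 2.04 | 53% | 17% |

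The 17% rises to 18% if 3M carries 51% of the weight.

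**Reliability of the 13-item version** (if three items of each sign are in the texts; the split is not stated)
- Negative, 6 items left: 6 × 0.561/(1 + 5 × 0.561) = 0.885.
- Positive: r = 0.86/(10 − 9 × 0.86) = 0.381; 7 items left: 7 × 0.381/(1 + 6 × 0.381) = 0.811.
- Attenuation of a standardized effect: √(0.885/0.92) = 0.98 and √(0.811/0.86) = 0.97, a loss of 2–3%.

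**The case against.** **Monitoring is part of STEP, so its effect is a treatment effect.** This holds where monitoring changes affect. It does not hold where monitoring changes only how an item is answered, and Aims 2 and 3 make claims about mechanism that depend on that difference.

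**This is ordinary SAP detail.** A sensitivity analysis could well stand in a SAP that is not shown, and nothing in the protocol is misstated. But the protocol itself fixes both the text content and the outcome instrument, and the one safeguard it gives covers the daily ratings only.

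**The size is assumed, and the only evidence is null.** This stands. The protocol gives neither size nor direction for a repeated-answering effect; closer mood tracking could also raise reported negative affect. The pilot used the same text procedures, with "mood responses based on the six Modified Differential Emotions Scale (mDES)(25) items delivered daily to STEP participants", and its self-report measures showed no significant difference between arms. With N = 52, that result is imprecise.

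**The reach is narrow.** This stands. H2A rests on implicit tasks and H2B on gratitude and life satisfaction. The eye-tracking and dot probe indices, IPANAT, GQ-6, SWLS and the primary clinical outcomes share no items with the texts.

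**Rescoring does not isolate the artefact.** This stands in part. A changed use of the scale or a wish to report progress could carry over to the other 13 items. That argues against replacing the planned subscale, not against showing the split.

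**Conclusion.** The item overlap and the one-arm exposure are clear from the protocol. What follows is a possible bias in one self-report instrument: an mDES difference at 3M or 6M could partly reflect familiarity with six of its 19 items. The firmest count is about 17–21 answered sets in the daily month against none in ETAU; 32–39 needs pilot rates to hold through the taper.

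A reader might infer that an mDES effect would be an artefact, or that the false-positive rate for H2C is as high as 53%. The documents support neither. The 6–53% and 4–17% ranges illustrate assumed shifts, all taken in STEP's favour, and their width shows how far they depend on those assumptions. Nor do the documents support dropping the planned subscales, or doubting Aim 2 as a whole or the clinical endpoints. The point is a low-cost improvement that limits what may be claimed from the rehearsed items.

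**What to change.** Keep the full mDES subscales as planned. For the self-report part of H2C, and for any mDES mediator in Aim 3, pre-specify a sensitivity analysis in both arms that scores 3M and 6M from only the 13 items not used in the texts, and show the six monitored items beside it. Name the six items. Add a rule of interpretation: a difference confined to the six monitored items is not reported as engagement or mediation. Settle this before any outcome data are seen by arm, so that the choice cannot look data-driven.

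The cost is some analysis and a few lines of text; no new data are needed. The 13-item version is shorter (alpha about .89 negative and .81 positive if three items of each sign drop out). It cannot remove a general shift in response style that affects monitored and unmonitored items alike, and the report should say so.
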